### Adverse events/harms

Adverse events are recorded using weekly self-report questionnaires consisting of five questions, distributed using REDCap software. Three questions are directed towards training-related adverse events: “has your knee given way (that is, in the same way as when you injured your knee) in connection with rehabilitation training with your physical therapist or on your own?”; “has your knee swelled up in connection with doing your rehabilitation training with your physical therapist or on your own?”; “have you experienced more pain in your knee in connection with your rehabilitation training with your physical therapist or on your own?” Two questions are related to adverse events in general (i.e., non-training related or overall): “have you had a new knee injury (that made it so you had to use crutches or undergo another surgery in your knee)?”; “have you had any other sickness (influenza, cold, etc.) or injury (sprained ankle, back pain) that resulted in not being able to do your rehabilitation training with your physical therapist or on your own?” Giving way episodes and new injuries which require further medical care are considered serious.

### Data management

Upon collection, data is checked by the SC and entered into a data file stored on a secure server. In cases of missing data, non-response, or questionable data, the SC contacts the participant to clarify. Data monitoring is done by NC on a regular basis, and any abnormalities are discussed with the research team (NC, SG, EA). Final data analysis will be informed by a statistician and performed by an unbiased third-party statistician.

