**Physical therapist**	
**Inclusion**	
- At least 2 years’ experience of treatment with training for musculoskeletal disorders	
- Treat patients with a knee injury on a weekly basis	

Clinics, as opposed to participants, are randomized in order to avoid familiarization with both conditions within the same clinic or the individual PT, a potential source of contamination which could influence intervention adherence and therefore skew results. In accordance with the Swedish health care system, participants select their clinic, and clinics do not actively advertise in order to recruit patients (making randomization at the participant level impossible), so self-selection of a treatment arm is theoretically random and blinded. PTs are given information on the methodology of their assigned intervention arm to allow them to recruit participants from their population.

Due to the nature of the design, as well as practical constraints (i.e., necessity of familiarity with intervention, staff availability), neither the study coordinator (SC), participants, nor PTs can be blinded. As a result, the test leader is blinded to the treatment condition and un-blinding is not permissible. Final data analysis is performed by a blinded third party in order to avoid potential bias.

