### Procedure

All knee injuries from the PTs patient pool are reported to the SC during weekly contact, in which the SC reminds PTs of inclusion criteria and actively seeks information on knee-injured participants in order to approach all potential participants in the patient pool. The number of patients approached and invited (i.e., eligible, ineligible, and declined participation) will be recorded. The SC contacts potential participants that have consented to a pre-screening interview, during which information is provided, inclusion, and exclusion criteria are verified, and, if eligible, the participant is invited to take part in the study. Information provided to potential participants includes only that there is a “mental training intervention” with no details which could be used to replicate the intervention, adhering to Swedish ethical guidelines for participant informed consent. Following pre-screening, the SC has regular contact with participants and physical therapists in order to receive updates on patient progression through rehabilitation. This ensures proper inclusion timing and reduces the risk of late inclusion by reducing dependency on physical therapists with regard to inclusion criteria, as well as ensuring that eligible participants are included in the trial. Rehabilitation during this period is provided according to rehabilitation protocols prescribed at the discretion of the PT until the participant is able to complete single-leg hop tasks, ensuring proper inclusion timing. When the hop ability criterion is confirmed by the PT, written information is provided, and baseline testing takes place, during which the test leader collects informed consent (Additional File 3 – Informed Consent Materials). The intervention then begins, implementing either CaU or MOTIFS training in the clinical setting during treatment. The intervention period is 12 weeks, as studies have shown that physical [28] and psychological [29] factors can be improved in this time span. MOTIFS training accounts for approximately 20 min [30] in a typical 60-min training session. At least 3 supervised or at-home training sessions are performed per week, whereof at least 6 are supervised by a participating PT during the intervention period, resulting in an intervention dose of 36 possible training sessions, with intensity prescribed by the PT. Participants and PTs are made aware of the possibility to end their involvement in the study. Participants may remove themselves at their discretion, or worsening symptoms may require the PT to change treatment strategy. To ensure that participants complete self-report questionnaires, telephone contact may be initiated.

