
#### Care-as-usual intervention

The control condition includes 12 weeks of “care-as-usual” training (CaU), in which participants receive treatment at the discretion of the participating PT according to commonly used neuromuscular training practices in physical therapy settings in southern Sweden. These typically aim to improve motor control and achieve dynamic stability in people with a knee injury [9]. Emphasis is on the quality and efficiency of movement, with little to no structured psychological training (Additional File 4: Appendix 1.3 [Appendix Table 1 – Care-as-Usual column]).

Participants in the CaU condition are contacted by the SC by telephone three times during the intervention period to ensure adherence to training and provide rehabilitation updates. This is done in order to maintain equal contact as compared with the MOTIFS condition.

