##### MOTIFS intervention

Care-as-usual rehabilitation exercises with integrated DMI constitute the MOTIFS model, the premise of which is that aspects of DMI are integrated into commonly used knee rehabilitation movements, as prescribed by the treating PT. The research team (NC, SG, GN, RD, EA) lead a workshop in which a PT specializing in neuromuscular training (GN) and a sport psychologist specializing in DMI (NC) train the physical therapists to deliver the MOTIFS training model. The workshop consists of a 5-h session in which physical therapists in the experimental group receive theoretical and practical instruction in the proper methodology of the MOTIFS model. Detailed information, including a film and a manual, is provided to aid in the effective implementation of the intervention in the clinical setting. It is also ensured that relevant equipment is available to patients (i.e. balls or sticks). Additional support workshops are held throughout the intervention period.

Participating PTs that have been educated on the implementation of the MOTIFS model explain, individualize, and administer the intervention to participants during face-to-face rehabilitation training sessions either individually or in small groups. This is supplemented by information and three face-to-face support visits by the SC with the patient, together with the PT, in order to allow for discussion and questions regarding the proper utilization of the MOTIFS model during supervised and at-home training sessions. These visits ensure proper patient fidelity and also assess whether the physical therapists are correctly using the MOTIFS model. Participants are instructed to train using the principles of the MOTIFS model, in which PT-prescribed physical exercises with simultaneous DMI are performed based on the participant’s desired activity-specific situation. MOTIFS training is applied in relevant situations and allows for separation between activity-specific functional movements and other aspects of rehabilitation that the PT deems necessary such as warm-up, strength training, balance training, mobility exercises, and/or cool-down.

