#### Outcome assessment

Physical and patient-reported outcomes are assessed at baseline and 12 weeks; patient-reported outcomes are assessed 12 months post-inclusion (Fig. 1). Prior to the testing occasion, self-report questionnaires are distributed using the REDCap electronic data capture tool [32], hosted by Lund University. Demographic data (age, gender, height, weight, treatment type, and injury history) and physical testing data (Table 3) are collected by an experienced test-leader either at the participants’ respective clinics or at the university lab according to a data collection form including testing procedures (further information is available in the data management plan, available at the ClinicalTrials.gov registration page: NCT03473821). Outcomes are assessed at 12 weeks post-inclusion to assess physical and psychological readiness when a PT would likely consider a return to activity testing, and at 12 months to assess long-term rehabilitation outcomes.

**Table 3 Tab3:** Outcomes assessment—description of types of outcome and the data used for analysis

Outcome		Type	Outcome data
Patient-reported outcomes	ACL-RSI^a^	12 item self-report scale (0–100 for each item)	0% (worst) to 100% (best) mean of summed total score
	KOOS	The normalized score for subscales: pain, symptoms, sports and recreational activity, activities of daily life, and quality of life	0 (worst) to 100 (best)
	PACES	18-item self-report scale (11 items reverse-scored)	18 (worst)–126 (best)
	PSS	10-item self-report scale	0 (best) to 40 (worst); 0–13 = low, 14–26 = moderate, 27–40 = high stress
	PEI	6-item self-report	0 (worst) to 12 (best)
	ROS	1-item self-report scale	Satisfied (3 or 2), mostly satisfied (1), or dissatisfied (0, −1, −2, or −3)
	RM	3-item self-report scale	0 (worst) to 10 (best); raw data presented
	TAS	3-item self-report scale (pre-injury, current, future)	1 (low activity)–10 (very high activity)
Physical testing	SH^a^	Number of completed hops	Change in the injured leg
	Hop test battery	SLHD-3 repetitions or until improvement <10cm; distance hopped (cm)	Change in the injured leg, change in the uninjured leg, LSI
		SH-number completed hops in 30 s	
	POEs	SLMS-5 repetitions; POEs assessed throughout the entire movement	Total POEs score
		SD-5 repetitions; POEs assessed on loading leg throughout entire movement until both feet are on the floor	
		FL-3 repetitions; POEs assessed on the front leg from landing until maximum flexion of the knee	

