#### Main outcomes

This trial includes two main outcomes. Psychological readiness to return to sport is evaluated using the Swedish version of the ACL-Return to Sport after Injury scale (ACL-RSI), which includes an emotional response, confidence, and risk-appraisal when returning to sport after an ACL injury [33, 34]. Physical function is evaluated using the change in number of hops in the injured leg from baseline to 12 weeks for the side hop task.

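### The unblinded study coordinator checks and queries collected data, and the self-reported main outcome ACL-RSI is not exempted

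*Protocol article*

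**What the plan says.** All references are to the protocol article.

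- **Data management:** "Upon collection, data is checked by the SC and entered into a data file stored on a secure server". It continues: "In cases of missing data, non-response, or questionable data, the SC contacts the participant to clarify". It does not define what makes a value questionable and excludes no variable.
- **Participants and randomization:** "neither the study coordinator (SC), participants, nor PTs can be blinded". The test leader is blinded, and a blinded third party performs the final analysis.
- **MOTIFS intervention:** participants in this arm receive "three face-to-face support visits by the SC with the patient, together with the PT".
- **Care-as-usual intervention:** "Participants in the CaU condition are contacted by the SC by telephone three times during the intervention period". The stated purpose includes keeping the amount of contact equal between arms.
- **Outcome assessment:** before each test occasion, "self-report questionnaires are distributed using the REDCap electronic data capture tool". The test leader collects the demographic and physical testing data.
- **Main outcomes and Table 3:** ACL-RSI, a 12-item self-report scale, is one of two main outcomes.
- **Procedure:** "To ensure that participants complete self-report questionnaires, telephone contact may be initiated". The caller is not named.
- **Discussion:** the coordinator's lack of blinding is listed as a limitation for recruitment and for nothing else.

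**The concern.** ACL-RSI items are opinions about confidence, emotion and risk, and the people giving them know their treatment. No external standard exists against which an answer can be found wrong, so following up an answered item as questionable is a matter of judgement. The plan gives the follow-up to someone who knows the arm and who, in one arm, has met the participant to support use of the intervention. A participant asked about a rating by that person may give the answer they think is wanted. The choice of which answers to follow up may also lean with expectation, without any intent.

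At stake is the credibility of one of the two main outcomes, and of the interim decision on continuing unmodified, which also uses ACL-RSI. The trial is described as assessor-blinded, but for this outcome the only assessor is the unblinded participant. A second unblinded influence on the same outcome is worth removing if that can be done cheaply.

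**Working it through.** No arithmetic applies, and the protocol gives no figure on queries or corrections to reproduce. The check is to follow an ACL-RSI answer from the participant to the analysis and ask at each step who handles it and what that person knows.

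1. **Entry.** The participant, unblinded, answers in REDCap before the test occasion (Outcome assessment). The test leader is not described as having a part in this.
2. **Checking.** The coordinator checks the data on collection (Data management). The coordinator is unblinded (Participants and randomization). Because clinics are randomized, the arm is known at baseline as well as at 12 weeks, so both ends of the change score pass through an arm-aware check.
3. **Query.** If something is missing, not returned or judged questionable, the coordinator contacts the participant (Data management). ACL-RSI falls within this wording because nothing is excluded.
4. **Relationship at the time of the query.** By 12 weeks the coordinator is scheduled to have had three contacts with each participant. They are in person and about using the model in MOTIFS, and by telephone about adherence and progress in Care-as-Usual. The number is balanced; the mode and content are not.
5. **Monitoring.** A member of the research team monitors the data and discusses abnormalities with the team (Data management). That member also helps train the MOTIFS physical therapists (MOTIFS intervention), and the monitoring is not described as blinded.
6. **Analysis.** A blinded third party analyses the file, after steps 2 to 5.

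Set against this path, the two stated safeguards miss the step in question. The blinded test leader protects the side-hop count, not the questionnaire. The blinded analysis protects against choices made with the final data, not against influence on the data before they reach the analyst. The limitation in the Discussion stops at recruitment.

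**The case against.** The strongest objection is that this is a condensed article pointing to a separate data management plan, where query triggers, audit trail and handling of corrections normally sit. That stands as far as it goes: the plan may already contain part of the remedy, and the absence of those details here is not the finding. What the article does state is who checks the data and who contacts participants, and it gives both tasks to an unblinded person without exempting outcomes.

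It can also be said that the queries cover all collected data, including weekly adherence and adverse-event surveys and injury history, where clarification is ordinary and useful. For ACL-RSI, blanks and non-returned forms are the likelier trigger than an odd rating. Participants are unblinded anyway, so reporting bias exists with or without the queries. Both points are fair and limit the likely size; neither is a reason to keep an avoidable second route.

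A reader might infer more than the text supports:

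- **That the coordinator enters the data or overwrites answers.** The sentence on entry is passive and names no one. Nothing says that an answered item is re-asked or that a clarified value replaces the submitted one.
- **That the coordinator delivers MOTIFS.** The physical therapists administer it. The coordinator's visits are held with the therapist, for support and to check fidelity.
- **That non-response will differ by arm.** Follow-up is described without distinction by arm and should reduce missing data. A differential effect is speculation.
- **That the bias can be sized against the 5-point ACL-RSI interim criterion.** That criterion is a difference between group means. Comparing it with a change in one participant's score mixes units, and any group-level shift would rest on invented rates of revision.

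**Conclusion.** The point holds as a statement of risk. The protocol gives checking and querying of all collected data to a coordinator who knows the arm and has in-person support contact with one arm only. ACL-RSI is not exempted, and neither stated blinding safeguard covers this step. The Discussion's limitation on coordinator bias is too narrow.

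The size is unknown and no figure should be attached to it. This is not evidence that any answer has been or will be changed. The conclusion rests on reading the Data management section as applying to all outcomes, as it is worded, and on the data management plan not already removing outcome questionnaires from coordinator queries. If that plan does so, what remains is to align the article's text with it and to widen the limitation. The change should be made, because it concerns a main outcome and costs little.

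**What to change.** In the Data management section and the data management plan:

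- Use ACL-RSI and all other questionnaire answers as submitted in REDCap, locked on submission, with range and required-field checks at entry.
- Send automated prompts for blank items and non-response, identically worded in both arms.
- Never re-ask a scale item that has been answered.
- Log any later correction as a separate value and keep it out of the primary analysis.
- Limit the coordinator's queries to non-outcome fields.

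In the Discussion, extend the limitation on the unblinded coordinator from recruitment to outcome data.

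Do not hand the calls to the blinded test leader. Participants know their arm and may disclose it, and the test leader collects the side-hop outcome; the protocol does not permit that person to be unblinded.

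The cost is REDCap settings, a short paragraph of text and possibly a few more missing items, for which the Data analysis section already sets missing-data rules. At the time of writing, 35 of about 106 participants had been included, so most answers were still to come. For those already included, the rule can be applied only where the submitted answer was kept, which the article does not say.

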## Discussion

The research team is composed of experts in physical therapy and sports medicine (EA), sport psychology (NC, SG), and clinically active physical therapists with a master’s degree and 10 (GN) and 26 (RD) years of clinical experience. This experience and expertise, along with consultations with other clinically active physical therapists, informed the research questions and training model. The model was tested on a range of physically active people with knee injury undergoing physical therapy rehabilitation and subsequently modified where appropriate. Further testing was done with patients until the model was deemed acceptable by both the research team and end-users (physical therapists, patients). Participating PTs in the study were also consulted in regards to recruiting for and executing the intervention, and changes were made to accommodate this. Interviews will be conducted with both PTs and patients to further explore the clinical relevance and applicability of the MOTIFS model.

The strengths of this trial include that it is randomized and pragmatic, exploring the MOTIFS model implemented under clinically relevant conditions experienced by end-users (i.e., both PTs and patients), as opposed to in a lab under ideal conditions. The MOTIFS model utilizes shared decision-making between the PT and the patient in order to create a unique care protocol based on the needs and desires of the individual that can be modified to fit any clinical rehabilitation setting. For this first RCT in which the MOTIFS model will be evaluated, patients in the later stage of rehabilitation are included. Principles of the MOTIFS model are applicable to patients in all phases of rehabilitation and in the treatment of other musculoskeletal injuries which may be the focus of future trials.

Limitations include that only the test leader is blinded to condition assignment due to the nature of the design. As the study coordinator is not blinded, bias cannot be ruled out during recruitment. Information to participants includes a brief description of the aims of the study in line with Swedish ethical guidelines, which may influence participants’ decision to participate or their behavior during the trial (i.e., if aware of a mental training intervention, more focus may be placed on mental aspects). However, as the participants receive no specific information, and imagery is assessed as a compliance measure, this is not seen as problematic. A further limitation includes that previous studies do not provide relevant data for sample size calculation. Mean differences, standard deviations, and variance are therefore theoretical, leading the authors to use an adaptive design in order to collect data which may be used for sample-size re-calculation. Simulation analyses, which may provide more accurate estimations, were not used to estimate sample size as these theoretical and estimated values would not provide reliable results. This highlights the adaptive nature of this trial and having collected data will provide information necessary to perform reliable sample size and power calculations for future research. This trial presents challenges in that it introduces the more holistic MOTIFS model, which shifts the clinical paradigm and places more focus on the individual and their context-specific needs from a psychological perspective. In order to aid in this, individual visits with the SC, as well as guidance and workshops, will smooth the transition to the novel MOTIFS training model.

Along with publication in a peer-reviewed journal, results of the study will be communicated via a popular science article in order to inform potential end-users of the outcome of this trial, with the aim of making the MOTIFS model readily available for use by end-users.

